#### Survey for Women

A questionnaire with closed-ended and open-ended questions will be used to explore women’s satisfaction with pushing, their childbirth experience, and their experience in joining the study. The researcher (JY) will access women during their stay in the postnatal ward for the completion of the survey. In case women withdraw from the study, for personal or medical reasons, a withdrawal note will be recorded in their CRF.

#### Focus Group With Midwives

The focus group with the midwives will form the qualitative part of the study. At the end of the intervention phase of the study, midwives will be invited to attend a face-to-face focus group to share their experience of supporting women with spontaneous pushing and their experiences of being part of the study. The discussion will be moderated by a senior researcher (HL) from the research team and will be guided by several open-ended questions.

As the primary objective of this study is to explore the feasibility of a future RCT, it is important to fully understand how midwives and women feel about the intervention, the procedure, and the enablers and barriers. The questions in the surveys for women and interviews for midwives will focus on the perceptions of both the women and midwives during the pushing phase of labor as well as their experience of being part of the study.

After a lengthy literature search, it was evident that there was no validated survey tool available that would meet the aims of this study. Therefore, the survey for women was developed based on the principles and domains advocated by Bowen et al [28], Section B “Childbirth Experience Questionnaire” in the survey for women is a freely available tool, which has been published in English and validated in Chinese by Zhu et al [29].

### Data Analysis

The data in this study include both quantitative and qualitative data. For quantitative data, “intention-to-treat” analysis will be used. Statistical description will be conducted by the description of mean value, SD, number of cases, and percentage. Pearson chi-square test will be conducted for categorical variables. Independent group 2-tailed *t* test will be conducted for continuous variables. The threshold for statistical significance will be set at .05. For qualitative data, a framework method will be used, which is commonly applied for the thematic analysis of interview transcripts [30]. After a verbatim transcription of the audio recording, the framework method will help to create and apply an analytic framework in the data analysis process in 5 steps (data familiarization, framework identification, indexing, charting, mapping, and interpretation) [31]. The quantitative and qualitative data will be combined in order to compile recommendations from the feasibility in order to conduct a future RCT.

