### Eligibility Criteria

The eligibility criteria for women and midwives are presented in Textboxes 1 and 2. The medical note audit will include women who received directed pushing during the second stage of labor and met the same eligibility criteria as the women in the spontaneous pushing group.

Eligibility criteria for women.

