### Recruitment

#### Recruitment of Women

The researcher (JY) will approach and recruit women into the study during their third trimester of pregnancy. This will allow the women to have enough time to read the information leaflet for the study, ask any questions, and make an informed decision about participating in the study without any undue pressure.

The study will be advertised using posters and information leaflets in the antenatal services of the hospital. The researcher (JY) will approach women while they are in the waiting room awaiting their appointment and will talk to them about the study assessing their willingness to receive further information about the study. Verbal information and a written information sheet outlining the study will be provided to the women to take home and review again before their next visit. At the women’s subsequent visit, the researcher (JY) will meet women who are willing to participate, provide them with an opportunity to ask any further questions about the research, and seek their consent to participate in the study by asking them to sign a consent form.

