#### Participants’ Safety and Withdrawal

A participant (including laboring women or midwives) may choose to withdraw from the study at any time. With consent, data before participant withdrawal will be retained and used in data analysis. Participant withdrawal may happen for several reasons, including but not limited to the following: (1) participant decision, (2) inability to comply with study procedures, and (3) the occurrence of what the participant perceives as an intolerable adverse effect.

In addition, the chief researcher (KB) will exclude a participant if it is considered necessary for any reason, including but not limited to (1) clinical decision, (2) ineligibility (either arising during the study or retrospectively having been overlooked at screening), (3) significant protocol deviation, and (4) significant noncompliance with intervention.

The nature and reason for the withdrawal or discontinuation will be recorded.

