#### Secondary Outcomes

Secondary outcomes will include the duration of the second stage of labor, maternal pushing position, mode of birth, rates of cesarean birth, perineal laceration, the rates of episiotomy, newborn Apgar scores, rates of newborn resuscitation, and rates of transfer to the neonatal intensive care unit. Table 5 illustrates the primary and secondary objectives, outcomes, criteria for success, methods for analysis, and measurement tools.

**Table 5 table5:** Primary and secondary outcome criteria, analysis, and measurement.

Objectives, outcomes, and criteria for success				Methods of analysis		Measurement or tool
**Primary objectives: To test the feasibility of a future RCT^a^ to compare the effects of spontaneous pushing and directed pushing for maternal and neonatal outcomes**						

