## Discussion

### Principal Findings

This is a protocol for a study assessing the feasibility, acceptability, and effectiveness of spontaneous pushing during the second stage of labor among Chinese women without epidural analgesia.

A challenge for this study may likely be the recruitment of laboring women. One of the exclusion criteria for women in this study is “administered epidural analgesia” (Table 3). A large proportion of recruited women may be excluded due to the use of epidural analgesia during labor. The epidural analgesia rate varies from one hospital to another in China [32]. However, the most recently noted rate within the study hospital was around 65% for primiparous women. Despite the anticipated high loss rate of laboring women, this exclusion criterion is set based on the underpinning midwifery philosophy that labor and birth under the use of epidural analgesia is not considered a physiological process. The International Confederation of Midwives [33] states that “Normal birth is where the woman commences, continues and completes labour with the infant being born spontaneously, in the vertex position at term, without any surgical, medical, or pharmaceutical intervention.” The use of epidural analgesia inhibits nerve conduction by blocking painful impulses from the nerves [34]. Although epidural analgesia is considered to be an effective way of pain relief in labor and birth [35], blocking of pain impulses also blocks other impulses conducted by the nerves, including pushing or bearing down urges. At the same time, the “intervention” in this study, spontaneous pushing, encourages laboring woman to feel their bodily urges and push in their most effective way. From this perspective, women who used epidural analgesia during labor may have difficulty feeling their pushing instinct, and hence, they are excluded from this study. The criteria of excluding women who used epidural during labor does not mean to influence women’s choices for their pain relief methods. The reasons for this criteria item will be explained beforehand to women to avoid their potential shame of the use of epidural analgesia during labor.

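### The analysis is labelled intention-to-treat, but enrolled women can be removed for deviation or noncompliance, a removal with no counterpart among controls chosen by treatment received

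*Protocol article*

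**What the plan says.** The Data Analysis section sets one rule for every quantitative outcome: "For quantitative data, “intention-to-treat” analysis will be used".

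Other sections of the protocol article decide who is left to analyse:

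- **Entry.** Under Recruitment of Women, the researcher is to "recruit women into the study during their third trimester of pregnancy", so enrolment precedes labor.
- **Exclusions known only in labor.** The eligibility criteria for women exclude epidural analgesia and cesarean birth during labor. Principal Findings confirms that enrolled women are affected: "A large proportion of recruited women may be excluded due to the use of epidural analgesia during labor".
- **Exclusions by the chief researcher.** Participants' Safety and Withdrawal lists grounds for removing a participant, ending with "3) significant protocol deviation, and (4) significant noncompliance with intervention".
- **Data kept.** The same section says: "With consent, data before participant withdrawal will be retained and used in data analysis".
- **Controls.** Under Eligibility Criteria: "The medical note audit will include women who received directed pushing during the second stage of labor". These women must meet the same criteria but are not recruited. Parity is the only stated matching factor (Participants).
- **Outcomes.** Secondary Outcomes lists "mode of birth, rates of cesarean birth, perineal laceration" among the effectiveness measures.

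**The concern.** Intention-to-treat means that a woman stays in the analysis once she has entered, whatever happens afterwards. Here a woman who enters and then departs from spontaneous pushing may be taken out. If women in whom the method was not sustained tend to have longer or more difficult second stages, their removal improves the intervention cohort's results. In a study described as noninferiority, that error runs in favour of the new strategy.

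Nothing matches this removal on the control side. A control is selected because she received directed pushing, so she cannot be noncompliant, and a routine-care woman who pushed spontaneously is never picked. One cohort is thus filtered after enrolment and the other is selected by treatment received, while the label tells readers that neither happened.

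At stake is the between-cohort comparison of labor outcomes. It is the use made of the control notes, and its second-stage duration is the outcome on which the sample size rests. Sample Size Determination also says that the study should yield estimates for sizing a future trial.

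**Working it through.** **1. The passages side by side.**

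| Event after enrolment | Intervention cohort | Control cohort |
|---|---|---|
| Epidural | excluded | excluded by the same criteria |
| Cesarean during labor | excluded | excluded by the same criteria |
| Deviation or noncompliance | may be excluded | no counterpart |
| Other pushing method used | may count as noncompliance | never selected |

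The first two rows are symmetric and the last two are not. With all rows applied, the intervention set is per-protocol-like. The retained-data sentence does not rescue the label: it concerns participant withdrawal, covers only data collected beforehand, and does not mention exclusion by the chief researcher.

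**2. Cesarean.** A birth that excludes the woman cannot also be counted as her outcome. With the criterion applied, the cesarean rate is driven towards zero in both cohorts.

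**3. The plan's own figure.** Sample Size Determination gives 105 per group, 90% power, α .05 and 20% dropout, but no effect, SD or margin, so 105 cannot be reproduced forwards. Back-solving:

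- Evaluable per group: 105 × 0.8 = 84.
- Detectable difference, two-sided .05: (1.960 + 1.282) × √(2/84) = 3.242 × 0.1543 = 0.50 SD.
- One-sided .05: (1.645 + 1.282) × 0.1543 = 0.45 SD.

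These serve only as a yardstick. The contradiction does not depend on them.

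**4. Shift from selective removal (assumed inputs).** The documents give neither a rate of noncompliance nor its link to duration. If a fraction f is removed and those women's second stage is D SD longer than that of the women kept, the mean of the kept women is below the mean of all by f × D:

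- f = 0.10, D = 0.5: 0.05 SD
- f = 0.10, D = 1, or f = 0.20, D = 0.5: 0.10 SD
- f = 0.20, D = 1: 0.20 SD

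**5. Near worst case (assumed).** If exactly the slowest fraction of a normal distribution is removed, the mean falls by φ(z)/(1 − f):

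- f = 0.10: z = 1.282, 0.1755/0.90 = 0.195 SD
- f = 0.15: z = 1.036, 0.2332/0.85 = 0.274 SD

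Against 0.50 SD, steps 4 and 5 together span 10% (0.05/0.50) to 55% (0.274/0.50) of the detectable difference.

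**6. Effect on the planned 2-tailed test.** With no true difference, 84 per group and an unchanged SD, the standard error is 0.1543 SD. A shift of 0.05 SD raises the rejection rate from 5% to about 6%, and a shift of 0.20 SD raises it to about 25%.

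**7. Reach into the primary outcomes (Table 5).** The completion criterion divides by all women recruited, so a woman removed for noncompliance counts against it. The questionnaire return rate divides by women who completed spontaneous pushing. The acceptability score states no such denominator.

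**The case against.** The strongest case on the other side has five parts.

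- **The same criteria apply to both cohorts.** This stands. A reader might infer that "administered epidural analgesia" as an exclusion makes the cohorts different populations. It does not by itself, because the audited notes must meet it too.
- **Keeping all recruits is not what the protocol intends.** This stands for epidural users: Principal Findings says plainly that they are out. A reader might fear a bias from epidural users in the intervention cohort only, but the text closes that route.
- **The primary outcomes are safe.** This largely stands. A reader might infer that the exclusions flatter feasibility. The documents do not support that: ratios over all recruited women absorb the exclusions, and reasons for withdrawal or discontinuation are recorded. The women's acceptability score is affected only if women who switched or were excluded were not surveyed, and the text does not say that they were not.
- **Selecting controls by directed pushing loses few women.** This is plausible, since directed pushing is the hospital default (Setting), and possible crossover is disclosed under Strengths and Limitations. It makes the control-side selection small but leaves the one-sided removal from the intervention cohort.
- **Effectiveness is exploratory, and an article leaves analysis-set detail to fuller documents.** The first half stands and lowers the severity. The second does not answer the point: the article itself states the label and itself states rules that contradict it.

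**Conclusion.** The point holds in a limited form. The protocol declares intention-to-treat for all quantitative data, yet provides for removal after enrolment on grounds that include noncompliance, and compares the remaining women with controls chosen by treatment received. The asymmetry lies in the deviation and noncompliance removal, which can favour spontaneous pushing. The cesarean exclusion separately empties a listed outcome.

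The size is unknown from the documents. The shifts of 0.05–0.20 SD, and of 0.20–0.27 SD near the worst case, rest on assumed removal rates, on an assumed link to duration and, for the second range, on a normal distribution. The 0.50 SD yardstick is back-solved with 84 per group and two-sided .05. None of these is an estimate of actual bias.

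The consequence falls on a secondary, exploratory comparison, so this should be fixed but does not undermine the feasibility objective.

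**What to change.** Reconcile the eligibility criteria for women, Participants' Safety and Withdrawal, Data Analysis and Principal Findings as follows.

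1. Report feasibility on all recruited women.
2. For the between-cohort comparison, set one start point in both cohorts: full cervical dilation, no epidural, and the other criteria met up to then.
3. Keep every enrolled woman who reaches that point, and every audited, non-enrolled routine-care woman who meets it, regardless of later deviation, noncompliance, pushing method or mode of birth. Define controls by non-enrolment and routine care, not by shift, because the trained midwives are rostered across all four shifts.
4. Limit removal from this set to withdrawal of consent or ineligibility arising before the start point.
5. Give the set an accurate name in place of intention-to-treat, and make per-protocol a sensitivity analysis.
6. Compute the acceptability score on all surveyed women who started, and state how many who switched were not surveyed.

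Data collection ended in October 2023, so further postnatal-ward surveys cannot be assumed. Labor outcomes come largely from medical notes (Case Report Form), so the analysis set can still be corrected without new participants. The cost is some extra extraction or re-audit of notes, and possibly slightly less favourable results.

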### Objectives

The primary objective is to test the feasibility of a future RCT to compare the effects of spontaneous pushing and directed pushing for maternal and neonatal outcomes. The secondary objective is to explore the effectiveness of spontaneous pushing and directed pushing for women without an epidural during the second stage of labor.

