### Sample Size Determination

One of the objectives of the feasibility study is to gain estimates for a sample size calculation in a future RCT [22]. Although a formal sample size calculation is not necessarily needed in a feasibility study, the sample size was calculated based on the duration of the second stage of labor as a parameter outcome in previous studies. Statistical power analysis was used to estimate sample size in PASS (version 15.0; NCSS LLC, USA) software with statistical power at 90%, α at .05, and dropout rate at 20%. The sample size was calculated to be 105 in each group. Based on clinical judgment and the number of laboring women eligible in the site-specific hospital, a sample size of 105 is set for each group.

To cover all 4 shifts of the roster, a total of 6 midwives will be recruited to deliver the intervention. All the midwives recruited to the study will be interviewed at the end of the study to assess midwives’ acceptability and experience participating in the study.

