	**Perineal laceration**					
		Intact, I degree, II degree, III degree, and IV degree	n (%) for categorical variables		Case report forms	

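### Perineal laceration is graded in five ordered steps but is assigned a Pearson chi-square test, which ignores the order: valid, but inefficient and silent on direction

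*Protocol article*

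**What the plan says.** - **Scale.** In Table 5 the perineal laceration entry reads "Intact, I degree, II degree, III degree, and IV degree", and its analysis column reads "n (%) for categorical variables".
- **Test.** The Data Analysis section says "Pearson chi-square test will be conducted for categorical variables" and "The threshold for statistical significance will be set at .05". It names no trend or ordinal test and no grouping of grades.
- **Status.** Laceration is listed under Secondary Outcomes. The Objectives section says: "The secondary objective is to explore the effectiveness of spontaneous pushing and directed pushing for women without an epidural during the second stage of labor".
- **Size.** Under Sample Size Determination, "a sample size of 105 is set for each group", and "the sample size was calculated based on the duration of the second stage of labor as a parameter outcome in previous studies". The same section names, as one objective, obtaining estimates for the sample size of a later randomised trial.

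**The concern.** The grades form a severity scale. A reader wants to know whether one pushing strategy goes with milder tears. A Pearson chi-square on a 2×5 table tests whether all five proportions are equal, on up to 4 degrees of freedom. Its statistic is unchanged if the grades are put in any other order, so part of its power goes to patterns unrelated to severity.

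There are two practical consequences. A real shift in severity is missed more often than it need be. And the p-value carries no direction and no effect size, although the study is meant to inform the sample size of a later trial.

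**Working it through.** **1. The plan's own figure.** The only sample size figure is 105 per group (90% power, alpha .05, 20% dropout), based on second-stage duration. No mean difference, SD or margin is given, so 105 cannot be reproduced. Back-solving, 105 × 0.8 = 84, and (1.960 + 1.282) × √(2/84) = 0.50 SD if the test is two-sided. No power is stated for laceration.

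**2. Inputs.** From the protocol: five ordered grades, 105 per group, alpha .05. Assumed, because the protocol gives none: the grade distribution under directed pushing, and a common odds ratio (OR) towards milder grades.

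**3. Why the order matters: one case by formula.** Assume Intact/I/II/III/IV of 20/50/28/1.5/0.5% and OR 2. Each cumulative odds is doubled; for Intact, 0.20/0.80 × 2 = 0.50, which gives 33.3%. The shifted distribution is 33.3/49.0/16.6/0.76/0.25%.

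The Pearson noncentrality is n × Σ(p − q)²/(p + q):

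105 × (0.0333 + 0.0001 + 0.0289 + 0.0024 + 0.0008) = 105 × 0.0656 = 6.9

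On 4 df this gives about 53% power. The same noncentrality on 1 df would give about 75%. The signal is almost all in the severity direction, and the extra degrees of freedom dilute it.

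**4. Simulation.** 20,000 trials per setting, uncorrected Pearson chi-square against a tie-corrected Wilcoxon test, two-sided .05, 105 per group, OR 2:

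| Assumed Intact/I/II/III/IV (%) | Chi-square | Wilcoxon | Gap (points) |
|---|---|---|---|
| 20/50/28/1.5/0.5 | 55.7% | 75.3% | 20 |
| 35/40/20/4/1 | 54.6% | 76.2% | 22 |
| 30/45/24/0.8/0.2 | 59.4% | 76.3% | 17 |
| 10/60/29.5/0.4/0.1 | 54.6% | 69.9% | 15 |
| 30/45/25, no III or IV | 66.6% | 76.2% | 10 |
| 30/69/1, nearly two grades | 60.2% | 68.9% | 9 |

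**5. Sensitivity to the effect size.** At 105 per group the gap is about 7 to 16 points at OR 1.5, 4 to 12 at OR 2.5, and 2 to 5 at OR 3. The largest gap in any setting was 23 points, at OR 2 with 84 per group and a wide spread of grades (20/30/30/15/5%). Chi-square had the lower power in every shifted setting.

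**6. Sparse cells.** In the case of step 3 the expected counts per group are 105 × (0.015 + 0.0076)/2 = 1.2 for III degree and 105 × (0.005 + 0.0025)/2 = 0.4 for IV degree, so 4 of 10 cells fall below 5. With no difference between groups and rare III and IV degree tears, chi-square rejects about 3 to 4% of the time and Wilcoxon about 5%.

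**7. Equal severity, different spread.** Take Intact/I/II of 30/40/30% against 20/60/20%. The first group is milder with probability 0.30 × 0.80 + 0.40 × 0.20 = 0.32. The second is milder with probability 0.20 × 0.70 + 0.60 × 0.30 = 0.32. At 105 per group chi-square rejects in 75% of trials and the rank test in about 5%.

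**The case against.** **The consequence is small.** The primary outcomes are feasibility and acceptability, judged descriptively or by framework analysis. Laceration has no success criterion, did not drive the sample size, and is compared without randomisation against medical notes matched on parity. Neither test would give a confirmatory p-value. This stands, and it makes the point minor.

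**The loss depends on assumptions, and grades may be merged.** This also stands. A reader might infer that the plan loses a fixed 20 points of power. The protocol supports no single figure, because it gives neither grade rates nor an effect size. Merging II to IV degree and keeping chi-square cuts the gap at OR 2 to about 9 to 11 points. The article neither states nor excludes such merging.

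**A false signal when neither strategy is better.** A reader might infer this from step 7. It is not an error of the test. The two distributions really differ there, chi-square is right to reject equality, and the n (%) per grade in Table 5 would show the pattern. Nothing in the protocol suggests that it will occur.

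**Sparse cells invalidate the test.** They do not; the error is on the conservative side.

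**Using 84 per group.** The comparison group is a set of selected medical notes, so dropout does not apply to it in the ordinary way. The main table therefore uses 105.

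**It can be left to an analysis plan.** The article does not leave the test open. It assigns one to every categorical variable, and Table 5 gives laceration that label.

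**Conclusion.** The point holds as a minor improvement. The plan assigns an order-blind test to an ordered outcome. The analysis is valid, but it is inefficient for a shift in severity and yields no direction or effect estimate. At 105 per group and a common OR of 2 the loss against a rank test is roughly 10 to 20 points: 15 to 22 if all five grades occur, 9 to 10 if only two or three do in practice. Across ORs of 1.5 to 3 and all settings tried it is about 2 to 23 points. These figures rest on assumed grade distributions and a proportional-odds shift. The feasibility conclusions are unaffected.

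**What to change.** In Data Analysis, add one sentence: perineal laceration grade is compared between groups with a Wilcoxon rank-sum test, or with a proportional-odds model reporting a common odds ratio and 95% CI. The model has the advantage of giving an estimate for the later trial. Keep n (%) per grade as description, and keep Pearson chi-square for unordered outcomes such as mode of birth.

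The article reports that data collection is finished and analysis was due to end by May 2024. The change should therefore be dated and recorded before the groups are compared, so that the choice of test does not depend on the results.

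It needs no new data or participants. There are two drawbacks. The common odds ratio assumes a roughly constant shift across grades. And a rank test can miss a pure difference in spread, which the n (%) per grade would reveal.

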**Methods:**

A nonrandomized, single-group, noninferiority feasibility study will be conducted in a public hospital in Hebei Province, China. In total, 105 women meeting the selection criteria will be recruited to receive the intervention (spontaneous pushing), while 105 sets of medical notes from women who received routine care (directed pushing) will be identified and reviewed to compare outcomes for both cohorts. A mixed methods approach will be used to assess primary outcomes (feasibility and acceptability) and secondary outcomes (effectiveness).

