## Methods

### Study Design

This feasibility study is a nonrandomized, single-group, noninferiority trial. All participants will receive the intervention (spontaneous pushing). A mixed methods approach will be used to assess the primary and secondary outcomes. This protocol adheres to the SPIRIT (Standard Protocol Items: Recommendations for Intervention Trials) guidelines (Multimedia Appendix 1) [21].

Table 1 illustrates the objectives, outcomes, and the corresponding study design. Tables 2 and 3 illustrate the chart of the study designs, visits, and assessments for both women and midwives. The flow diagram (Multimedia Appendix 2) demonstrates the enrollment, allocation, follow-up, and assessment process for women to compare the effectiveness of the intervention.

**Table 1 table1:** Objectives, outcomes, and study design.

Objectives and outcomes		Study design
**Primary objective: To test the feasibility of a future RCT^a^ to compare the effects of spontaneous pushing and directed pushing for maternal and neonatal outcomes**		
	Feasibility: recruitment rates, retention rates, and attendance rates of participants	Quantitative study design
	Acceptability: women’s and midwives’ perspectives and acceptability of the intervention	Quantitative study design (survey for women) and qualitative design (interviews for midwives)
**Secondary objective: To explore the effectiveness of spontaneous pushing and directed pushing for women without an epidural during the second stage of labor**		
	Maternal and neonatal outcomes	Quantitative study design

^a^RCT: randomized controlled trial.

**Table 2 table2:** Chart of the study design, visits, and assessment for women.

Time point			Visit 1: during late pregnancy at clinics		Visit 2: at clinics or admission to the prenatal ward		Visit 3: during the second stage of labor		Visit 4: within 2 hours after birth		Visit 5: during the stay in the postnatal ward

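### The study is labelled noninferiority, but the only between-cohort tests it fixes look for a difference and cannot establish noninferiority, so a non-significant result could be misread as not worse

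*Protocol article*

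**What the plan says.** **The label.** The title describes a noninferior feasibility study. The abstract's Methods paragraph says: "A nonrandomized, single-group, noninferiority feasibility study will be conducted in a public hospital". The Study Design section repeats it: "This feasibility study is a nonrandomized, single-group, noninferiority trial".

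**The analysis.** The Data Analysis section names two between-cohort tests: "Pearson chi-square test will be conducted for categorical variables. Independent group 2-tailed" t test, the latter for continuous variables. It adds: "The threshold for statistical significance will be set at .05". It also specifies intention-to-treat and descriptive summaries. Table 5 lists only descriptive summaries for the effectiveness outcomes.

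**The sample size.** The Sample Size Determination section bases the calculation on duration of the second stage and gives "statistical power at 90%, α at .05, and dropout rate at 20" per cent, arriving at 105 per group. It states no difference, SD, margin or sidedness.

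**The status of the comparison.** The Objectives section makes feasibility of a future randomized trial the primary objective. The effectiveness comparison is secondary and exploratory.

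**The concern.** A noninferiority design asks whether the new strategy is worse by no more than a stated amount. Its null hypothesis is that the strategy is worse by at least that amount, and the usual evidence is a confidence limit lying on the right side of the margin. Pearson chi-square and a two-tailed t test have a null hypothesis of no difference. Rejecting that null shows a difference, and failing to reject it shows nothing about a margin.

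Under the tests as written, no result can support the claim that the design label announces. The nearest result is p>.05, which is easier to obtain with fewer or noisier data. A reader who takes the label from the title and then sees non-significant comparisons of duration, perineal or neonatal outcomes could conclude that noninferiority had been shown.

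**Working it through.** **1. Can the stated 105 be reproduced?** The inputs are 90% power, α .05, 20% dropout and 105 per group (Sample Size Determination). No difference, SD, margin or sidedness is given, so the figure cannot be rebuilt forwards. It can be solved backwards.

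- Evaluable per group: 105 × 0.8 = 84.
- Standardised difference or margin (normal approximation): d = √(2/n) × (z for α + z for power).
- Two-sided .05 or one-sided .025: √(2/84) × (1.960 + 1.282) = 0.1543 × 3.242 = **0.50 SD**.
- One-sided .05: 0.1543 × (1.645 + 1.282) = **0.45 SD**.

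**2. Does 105 reveal which design was powered?** Forwards, with an assumed d of 0.50 SD: n = 2 × 3.242² / 0.50² = 84.06. Rounded up this is 85, or 107 after dividing by 0.8; 84 unrounded-up gives exactly 105. A two-sided difference test at 0.50 SD and a noninferiority test at one-sided .025 with a 0.50 SD margin and true difference zero give the same number. A noninferiority test at one-sided .05 with a 0.45 SD margin also gives 85, hence 107. So 105 is compatible with either design and does not resolve the mismatch.

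**3. How often is the two-tailed test non-significant when the intervention is truly worse?** The probability of non-significance is 1 − power of the two-sample t test, with noncentrality d × √(n/2). For n = 84, √(84/2) = 6.481. The effect sizes are assumptions; none is in the document.

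| Assumed true lengthening | Noncentrality | p>.05, 84 per group | p>.05, 105 per group |
|---|---|---|---|
| 0.25 SD | 1.62 | 64% | 56% |
| 0.30 SD | 1.94 | 51% | 42% |
| 0.50 SD | 3.24 | 10% | 5% |

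**4. Do the two decision rules really disagree?** With 84 per group, the half-width of a 95% confidence interval is 1.96 × √(2/84) = 0.30 SD. A two-tailed test is non-significant when the observed lengthening is below about 0.30 SD. With an assumed margin of 0.50 SD, noninferiority needs an observed lengthening below 0.50 − 0.30 = 0.20 SD. An observed lengthening between 0.20 and 0.30 SD is therefore non-significant and yet fails that noninferiority criterion. For example, 0.25 SD gives an interval of −0.05 to 0.55 SD.

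**The case against.** The strongest reply has four parts.

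- **The interpretation is not in the document.** A reader might infer that the authors will treat p>.05 as proof of noninferiority. Nothing says so. The Results section speaks of exploring effectiveness, and the Data Analysis section says the data will inform recommendations for a future trial. This stands: the risk is a possible misreading, not a written rule.
- **The comparison is secondary.** A reader might infer that the study's main conclusion is at risk. It is not. The feasibility and acceptability criteria in Table 5 do not depend on the t test or chi-square, and no success threshold is attached to the effectiveness outcomes. This stands and limits the weight of the point.
- **A condensed article may leave the margin and interval rule to a fuller document.** This stands for the absence of those items, and for the absence of a per-protocol analysis, which in an exploratory comparison is a preference. It does not answer the mismatch: the article does fix its tests, sidedness and threshold, and those are not noninferiority tests.
- **The illustration depends on assumed effects.** This stands. At the back-solved 0.50 SD the chance of non-significance is only about 10%.

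A reader might also apply the 65% epidural rate in the Discussion to all 105 recruited women, leaving about 37, and obtain larger probabilities. The document does not support that: the 65% is given for primiparous women only, while multiparous women are also enrolled and are assumed to use epidurals less.

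**Conclusion.** The mismatch is real and lies within the protocol article: a noninferiority label in three places, and only tests of no difference in the analysis. A non-significant result could be misread as evidence that spontaneous pushing is not worse. How likely such a result is under true worsening depends on assumed values: about 64%, 51% or 10% for 0.25, 0.30 or 0.50 SD. These rest on 84 evaluable per group, equal variances and a two-sample t test. The point is confined to an exploratory secondary comparison and is a matter of correct labelling and reporting.

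**What to change.** Choose one of two routes, according to what was entered in PASS.

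- **A margin was entered before data collection.** State it with its SD and sidedness. For duration of the second stage, replace the significance test by the confidence interval for spontaneous minus directed pushing: two-sided 95% if the calculation used one-sided .025, 90% if it used one-sided .05. Compare the upper limit with the margin, and present the result as exploratory, from a nonrandomized comparison.
- **No margin was used.** Do not choose one now, since data collection ended in October 2023. Remove the noninferiority wording from the title, abstract and Study Design section, report between-cohort differences with 95% confidence intervals as exploratory, and state that p>.05 is not evidence of noninferiority.

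Either route changes wording and the form of reporting only. No new data are needed. The article plans to complete analysis by May 2024, so the change fits before results are reported.
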